### Objectives

The aim of this pilot study is to test the feasibility, acceptability and preliminary efficacy of the Aumio app and the parent-centred email psychoeducation module. We aimed (1) to examine the feasibility and acceptability of the of the Aumio app and the parent-centred email psychoeducation module. We therefore aimed to conduct qualitative and quantitative data to gain comprehensive insights. In addition, we also aimed (2) to collect information for improvements of the Aumio app and the parent-centred email psychoeducation module from a user’s perspective. We furthermore aimed (3) to examine the preliminary efficacy of the Aumio app and the parent-centred email psychoeducation module. As secondary user-centred outcomes, we aimed to examine whether its use improves children’s sleep, covering a broad range of facets to adequately capture the multidimensional nature of sleep. Furthermore, preliminary efficacy on child’s health-related quality of life and effects on parental stress will be tested as secondary user-centred outcomes. In order to further improve the feasibility and to synthesize recommendations for use, it will be investigated (4) at which intensity of usage the Aumio app significantly affects the feasibility and satisfaction as well as the secondary user-centred outcomes. The intensity of usage will be analysed continuously as well as divided into 4 levels (12, 18, 24, and 30 uses during the study period) and included in the analyses.

The primary, feasibility hypothesis refers to the user’s subjective perspective on the Aumio app and the parent-centred email psychoeducation module, with the assessment time points 6 weeks after the start of the app use, at the midpoint of the 12-week parent-centred email psychoeducation module and again another 6 weeks after. We hypothesize that the Aumio app and the parent-centred email psychoeducation module is feasible. We also hypothesize Aumio app and the parent-centred email psychoeducation module is accepted among the users. We further hypothesize that the present study design is feasible to conduct a large scale trial on the effectiveness.

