### Sample size

With regard to the required sample size, two factors were considered in the present study: The Aumio app for the children and the parent training. For the parent training, we first considered effects on child outcomes as a basis for sample size calculation. An average effect size of parent training of d = 0.20 was found in a meta-analysis on the effectiveness of family-based prevention interventions [31]. An average effect size of d = 0.21 of universal prevention programs was found in a meta-analysis on German-language effectiveness research [32]. Based on these findings, with an assumed power of.90, an alpha error level of.05, and an effect size of.21, a required sample size of 196 was calculated using the software g*Power [33].

Considering the drop-out rate (DOR) observed in the unpublished master’s theses on the Aumio app, this was also considered for sample calculation. In one of the most recent master’s theses on the effectiveness of the Aumio app, a drop out of 57.14% was found in the treatment group. Based on an expected DOR of 0.57, the number of cases is multiplied by the correction factor 1/(1-DOR) [34]. If the previously calculated sample size is increased by the expected DOR, a final required sample size of 456 is needed.

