### Statistical methods

#### Statistical methods for primary and secondary outcomes.

Descriptive methods including the calculation of appropriate summary measures of the empirical distribution (mean, standard deviation, median, minimum and maximum for continuous variables, and frequency in percentages for categorical variables) and specification of missing observations are used to present socio demographic data, feasibility, acceptability (with the Aumio app and the email course) and data on app use. In addition to the quantitative analysis of feasibility and acceptability, open-ended responses will be examined for recurring themes and categorized in a structured manner to provide additional context and insight into user experiences.

Preliminary intervention effects on the outcomes are analyzed by repeated measures ANOVA. Furthermore, the study will explore the relationship between the intensity of use and the outcomes. This analysis will involve both app usage as continuous measure, and categorization of the intensity of use into four levels (e.g., 12, 18, 24, and 30 uses during the intervention period). We will assess whether significant effects on the outcomes are observed at different levels of app use. All statistical analyses will be performed using R.

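### Objective 4 looks for the usage level at which effects are significant; significance within levels does not show that levels differ and can easily yield a usage threshold that does not exist

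*Protocol article*

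**What the plan says.** The Objectives section of the protocol article gives the fourth aim as finding "at which intensity of usage the Aumio app significantly affects the feasibility and satisfaction as well as the secondary user-centred outcomes". The stated reason is to improve feasibility and to arrive at recommendations for use. Usage is to be analysed continuously and also "divided into 4 levels (12, 18, 24, and 30 uses during the study period".

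The section on statistical methods for primary and secondary outcomes names repeated measures ANOVA for the intervention effects. It then says that usage will be explored both as a continuous measure and in four levels, with 12, 18, 24 and 30 uses now given only as examples. The operative sentence follows: "We will assess whether significant effects on the outcomes are observed at different levels of app use".

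The text preceding the Methods labels the usage analyses exploratory. Neither section names a usage-by-time or level-by-time test, and neither says which usage analysis the recommendations will rest on. The sample size section plans for one overall effect and gives no size per level.

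**The concern.** Both sentences attach significance to a level. Neither asks whether the effect differs between levels. A pre-post change that reaches p < .05 at 24 uses but not at 18 does not show that 24 uses do more than 18. The p-value within a level depends on how many families fall in it as well as on the size of the change.

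What is at stake is the product of the fourth aim. Over 12 weeks, 12, 18, 24 and 30 uses are 1, 1.5, 2 and 2.5 uses per week. The intervention section already advises use at least twice a week, so the result bears directly on advice that families receive. A recommendation read from the pattern of significant levels could reflect little more than level sizes and chance.

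**Working it through.** **Inputs from the sample size section.** The effect size rests on this statement: "An average effect size of d = 0.21 of universal prevention programs was found". Power is set at 0.90 and alpha at .05. The result is given as "a required sample size of 196 was calculated using the software g*Power". The inflation for dropout is 1/(1 - 0.57).

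**The plan's own figure.** Exact power of a paired t test uses the noncentral t distribution with n - 1 degrees of freedom and noncentrality d√n. At d = 0.21 and alpha = .05:
- n = 196 gives power 0.901 one-sided and 0.833 two-sided. Two-sided, 241 would be needed for 0.90.
- So 196 reproduces as a one-sided calculation. Sidedness is not stated, and both versions are shown below.
- 196/0.43 = 455.8, which rounds up to 456.

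**Assumptions.** The sizes per level are not in the document. The base case is 196/4 = 49 per level. The true change is d = 0.21 in every level, so usage makes no difference. The levels are separate bands, each tested on its own.

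**Power per level.** The noncentrality is 0.21 × √49 = 1.47. Power p is 0.302 two-sided and 0.422 one-sided.

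**Some but not all levels significant:** 1 - p⁴ - (1 - p)⁴.
- Two-sided: 1 - 0.008 - 0.237 = 0.754.
- One-sided: 1 - 0.032 - 0.111 = 0.857.

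**Threshold pattern (lowest level not significant, at least one higher level significant):** (1 - p)[1 - (1 - p)³].
- Two-sided: 0.698 × (1 - 0.340) = 0.461.
- One-sided: 0.578 × (1 - 0.193) = 0.466.

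**Clean step (not significant up to some level, significant at every level above it):** 17% two-sided, 18% one-sided.

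**Other level sizes, uniform d = 0.21:**

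| Families per level | Mixed pattern, two-sided | Mixed pattern, one-sided |
|---|---|---|
| 49 each | 75% | 86% |
| 39 each (a fifth group has fewer than 12 uses) | 68% | 82% |
| 80/50/36/30 | 76% | 87% |
| 114 each (all 456, treated as fully observed) | 84% | 73% |

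With 80/50/36/30 and the lowest level the largest, the threshold pattern falls to about 31%. Two-sided: 0.542 × (1 - 0.693 × 0.768 × 0.801) = 0.311.

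If the levels are cumulative cut-offs (at least 12, at least 18, and so on), simulation gives mixed patterns in 55-72% of trials. Significance then tends to be lost at the higher cut-offs, where fewer families remain.

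**Other uniform effects, 49 per level:**

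| d | Mixed pattern, two-sided | Mixed pattern, one-sided |
|---|---|---|
| 0.30 | 87% | 79% |
| 0.40 | 62% | 43% |
| 0.50 | 26% | 14% |
| 0.80 | about 0% | about 0% |

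With no effect at any level, the chance of at least one significant level is 1 - 0.95⁴ = 18.5%.

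**Direct comparison.** In simulation with n = 196 and uniform d = 0.21, a false usage effect appears in 5.0% of trials with a four-level interaction test and in 4.7% with a continuous-usage slope.

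**The case against.** **Continuous usage is already planned.** The sentence just before the operative one says so, and the Objectives agree. A reader might infer that the plan has no dose-response analysis; that would be wrong. What is missing is priority: nothing says that the continuous analysis, rather than the pattern of significant levels, decides the recommendation.

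**Separate tests within levels are not stated.** The levels are to be included in the analyses, which also fits a usage factor in the repeated measures ANOVA. Satisfaction is surveyed only after app use has begun, so it has no baseline, and a pre-post test within levels cannot serve all of Objective 4. This stands as a caution. Even so, asking at which intensity the effect is significant reads most naturally as significance level by level. The exact model may be left to an analysis plan, but the criterion is stated here, and a plan that followed it would inherit the problem.

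**The effect may be larger than 0.21.** The figure comes from meta-analyses of prevention programmes, and the Discussion warns that designs without a control group give overly optimistic effect sizes. This stands: at d = 0.5 with equal levels the problem is much smaller.

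**The analysis is exploratory, in a pilot.** This stands and lowers the severity. It does not remove the concern, because recommendations for use are the declared output.

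**Families with fewer than 12 uses.** A reader might infer that they are excluded and numerous, given the expected dropout. The document does not say whether 12, 18, 24 and 30 are lower bounds, upper bounds or cut-points, and the 57% is dropout from an earlier thesis, not a usage distribution. Only the conditional point holds: if the levels are bands starting at 12, low users have no level.

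**Conclusion.** The concern holds in a limited form. As worded, Objective 4 and the methods sentence make significance at a level the criterion, and this cannot show that usage changes the effect. On the plan's own d = 0.21 and 196 completers, with an assumed 49 per level and no true difference between levels, a mixed pattern arises in about 75% (two-sided) to 86% (one-sided) of trials, and in 68-87% across the other splits tried.

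A reader might go further and infer that three of four trials would report a threshold. The figures do not support that, because a mixed pattern includes, for example, a single middle level being significant. The threshold pattern occurs in about 46-47% per outcome with equal levels, and a clean step in 17-18%. The fair statement is that the rule can easily report a threshold that does not exist.

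The result rests on assumed level sizes, on reading the levels as separately tested, and on a pre-post change near 0.21. The severity is moderate, because the analysis is exploratory and no primary or secondary hypothesis depends on it.

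**What to change.** Replace the sentence on significant effects at different levels, and align the wording of Objective 4:

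- Base Objective 4 on the continuous usage analysis already planned, as a usage-by-time term with a non-linear term, or on a level-by-time interaction. State which one decides.
- For satisfaction, which has no baseline, estimate its association with usage.
- Report each level's mean change and the between-level differences with confidence intervals, as description.
- Define the levels as bands, include one for families with fewer than 12 uses, and fix the cut-offs in both sections.
- State that recommendations rest on the dose-response estimate and not on which level reaches p < .05. That estimate should be read as an association, because families choose how much they use the app and there is no control group.

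The cost is analysis wording only, with no new data and no change in sample size. The drawback is that the result is less quotable than a single cut-off.

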#### Interim analyses.

No interim analyses on treatment effectiveness will be conducted

### Methods for additional analyses

Additional analyses will be conducted to examine whether effects differ between groups with different sociodemographic characteristics, e.g., household size, parental education, parental income, relationship conflict between parents, parental separation, co-sleeping and media use. We will therefore evaluate the effects of including sociodemographic characteristics as covariates in an analysis of covariance (ANCOVA).

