### Trial design and study setting and participant timeline

The present research project is designed as a one-group pre-post pilot study. As this trial is the first larger scale pilot trial on the feasibility and acceptability as well as the first trial on the preliminary efficacy of the app on sleep quality and the parent module, randomization, control groups, and blinding do not apply to the study design of this trial. The study is a single study conducted in the naturalistic setting of the app, meaning it was conducted exclusively in-app and within a German-speaking population. After consenting to participate in this study, the participants will be provided a 12-months free access to the Aumio app and receive the parent-centred email psychoeducation module at weekly intervals.

Once participants agree to the conditions of participation and meet the inclusion criteria, guardians are directed to the first assessment (T0). At T0, at the beginning of the intervention and before the first app use, data on sociodemographic characteristics and relevant covariates and the outcomes will be collected. After completing the first survey T0, participants are provided with free access to the Aumio app for one year and receive the parent-centred email psychoeducation module once a week. The intervention duration is set at twelve weeks. Six weeks after the intervention start and the first app use, the second measurement point (T1) takes place, where primary and secondary outcomes are assessed. Immediately following the conclusion of the 12-week intervention, the third measurement point (T2) is conducted, comparable to the T1 assessment (Fig 1).

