### Sociodemographic variables and covariates

At T0, sociodemographic characteristics and relevant covariates that have been identified in advance through a literature review are collected, including household size (“How many people live in your household all the time, including yourself?”, “Do other children live in your household besides the child with whom you are participating in our study?”; [24]), parental education (“What is your highest educational achievement?”; [24]), parental income (“Approximately what is the total average monthly net income of your household?”; [25]), relationship conflict between parents and parental separation (“Which marital status describes you best?”, “How would you describe your satisfaction with your relationship?”; [26,27]), sleeping together in the same bed (assessed through the SI-KJ; [28], child media use before bedtime (“How often does your child use electronic media before sleeping?”, “What electronic media does your child use before sleeping?”; [29]), and presence of media in the child’s sleep environment (“Is there electronic media in your child’s room?”, “What electronic media is in your child’s room?”; [30]). Covariates are assessed by categorial variables.

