Lastly regarding the analysis of the preliminary efficacy, the study design of the present research project, the single-group pre-post design, must be considered critically in itself. The methodological weaknesses were summarised by Maier-Riehle and Zwingmann [39]. First, the effect sizes cannot be interpreted causally because the observed changes are not exclusively attributed to the intervention but also to other confounding causes. In addition, different calculation methods are proposed for determining effect sizes in the single-group pre-post design. As a result, effect sizes are not comparable among each other and lead to different patterns of results. Last, it should be noted that Cohen’s limits of interpretation cannot be invoked when interpreting effect sizes, as these are based on independent samples and provide an overly optimistic measure in designs without a control group. No alternative limit of interpretation for effect sizes in single-group pre-post designs has been established at this time [39]. Nevertheless, the inclusion of covariates which possibly influence the primary and secondary outcomes aims to provide a more detailed picture of the preliminary efficacy of the Aumio app and can further prepare a larger, RCT with the focus on testing the efficacy of the Aumio app.

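### The plan asks whether pre-post effects differ between sociodemographic groups, but including the characteristics as ANCOVA covariates, as worded, tests average level rather than change

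*Protocol article*

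**What the plan says.** The design section states: "The present research project is designed as a one-group pre-post pilot study". Under the statistical methods for primary and secondary outcomes, "Preliminary intervention effects on the outcomes are analyzed by repeated measures ANOVA". An effect in this trial is therefore a change over time within families.

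The section on methods for additional analyses sets the question: "Additional analyses will be conducted to examine whether effects differ between groups with different sociodemographic characteristics". Its examples include household size, education, income, separation, co-sleeping and media use. The next sentence gives the method as a consequence of that question: "We will therefore evaluate the effects of including sociodemographic characteristics as covariates in an analysis of covariance (ANCOVA". The section names no interaction with time, no change score and no dependent variable.

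The Discussion describes the same analysis as "the inclusion of covariates which possibly influence the primary and secondary outcomes aims to provide a more detailed picture of the preliminary efficacy". That is the language of adjustment or prediction. The section on sociodemographic variables and covariates adds that "Covariates are assessed by categorial variables", and that they were chosen beforehand from a literature review.

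**The concern.** The question is one of effect modification: does the change from T0 depend on the characteristic? The stated method is covariate inclusion. In a repeated measures model, the term for a characteristic fixed at T0 compares the groups' means averaged over all time points. It does not ask whether the groups moved differently.

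Including the characteristic does not sharpen the main result either. There is no treatment arm to adjust, and with complete data an additive between-person covariate leaves the within-person time contrasts as they were. Comparing the model with and without covariates would say nothing about who responded.

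The covariates were selected as relevant, so level differences between groups are plausible. A group that sleeps worse throughout could be reported as responding differently, and a group that responds better could go unnoticed. The Discussion says the results will inform a later randomised trial and presents the covariate analysis as part of that preparation.

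**Working it through.** **The plan's own figures.** Only the number of completers is used below. The sample size section works "with an assumed power of.90, an alpha error level of.05, and an effect size of.21". A paired t-test with these inputs (noncentral t) needs 196 one-sided, which matches, and 241 two-sided. With 57% dropout, 196 / (1 − 0.57) = 196 / 0.43 = 455.8, so 456, which also matches. Neither figure is disputed here.

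**Assumptions not in the documents.** Two equal groups (98 each), SD 1 at each time point, correlation r = 0.5 between any two time points, two-sided 5% tests, and any change fully present at T1 and kept at T2. The value 0.42 SD is a case in which one group changes by 0.42 and the other by 0, so the average is the planned 0.21.

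**Standard errors of the group difference.**
- Covariate term (person mean over three time points): variance (1 + 2r)/3 = 0.667, SE = √(0.667 × 2/98) = 0.117.
- Interaction as T2−T0 change: variance 2(1 − r) = 1, SE = √(2/98) = 0.143.

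Approximate power is Φ(difference/SE − 1.96).

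**Case 1: level differs by 0.4 SD, change is equal.**
- Covariate term: 0.4/0.117 = 3.43, Φ(1.47) ≈ 93%.
- Interaction: the true difference is 0, so it rejects at 5%.

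**Case 2: change differs by 0.42 SD, mean level over time is equal.** One group starts 0.28 SD lower and ends 0.14 SD higher: (−0.28 + 0.14 + 0.14)/3 = 0.
- Covariate term: true difference 0, rejects at 5%.
- Interaction: 0.42/0.143 = 2.94, Φ(0.98) ≈ 84%.

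**Case 3: change differs by 0.42 SD, baselines are equal.** The mean level then differs by (0 + 0.42 + 0.42)/3 = 0.28.
- Covariate term: 0.28/0.117 = 2.40, Φ(0.44) ≈ 67%.
- Interaction: 84% by formula.

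**Simulation (4,000 runs per case).** Case 2 gave 5% and 84%; case 3 gave 67% and 83%. With a level difference of 0.5 SD and equal change, the covariate term rejected 99% and the interaction 5%.

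**Modelling T2 on T0 plus the characteristic.** In that last setting this model rejected 49%. With r = 0.5 it removes only half of the baseline gap and leaves 0.5 − 0.5 × 0.5 = 0.25 SD. It tests a baseline-adjusted difference, which is a different quantity.

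**Power of the interaction for a smaller difference.** For 0.21 SD: 0.21/0.143 = 1.47, Φ(−0.49) ≈ 31%.

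**The case against.** The strongest reply is that the section never states the model. It names no dependent variable and neither includes nor excludes an interaction. In a one-group study, an ANCOVA on the change score would make the characteristic's own coefficient the test of whether effects differ, and a repeated measures ANCOVA can also yield a time-by-covariate term. A reader might infer that the plan cannot test its question, or that it will give a wrong answer. The documents do not support that; they support only that it can, under the reading their wording suggests.

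Case 2 is also a special pattern: the groups must start apart and cross. With equal baselines (case 3), the covariate term picks up part of the difference, so real differences in response are not always missed. Several characteristics would probably have more than two categories, and the equal split is assumed.

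Finally, these are additional analyses for which the sample was not sized, the Discussion already warns against causal reading, and a condensed article may leave model terms to a fuller document. That limits the weight of the point but does not remove it. The article states both a question and a method, the second is offered as the answer to the first, and the Discussion leans towards adjustment. A stated method that does not match its stated question is more than an omitted detail.

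**Conclusion.** The point stands as a mismatch between question and stated method. Put into the repeated measures model without a time interaction, the characteristics test level, not change. Under the assumptions above, the covariate term then rejects about 93% when only level differs by 0.4 SD. It rejects about 5% when change differs by 0.42 SD with equal mean level, where the T2−T0 interaction contrast rejects about 84%. With equal baselines the gap narrows to 67% against 83%.

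These rates illustrate how far the two tests can diverge; they do not predict this trial's data. They rest on 98 per group, r = 0.5 and complete follow-up of 196. The primary feasibility outcomes and the main pre-post analysis are not affected.

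**What to change.** Replace the ANCOVA sentence in the section on methods for additional analyses with:

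*Differences in effect are tested by the characteristic × time interaction in the repeated-measures (mixed) model, reported as the difference in T2−T0 change with 95% CI; these tests are exploratory.*

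A model of T2 on T0 should not be offered as interchangeable with this.

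The cost is one sentence, with the same data and the same software. The downside is low power, about 31% for a 0.21 SD difference in change, so the results should be presented as estimates with intervals, and a non-significant interaction should not be read as evidence of equal effects.
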